90-day acute renal failure-related hospital readmission	–	–
90-day emergency department visits	–	–
90-day acute care-free days alive	–	–
90-day acute care costs	–	–
90-day total healthcare costs^a^	–	–

*IMPACTS* Improving Morbidity during Post-Acute Care Transitions for Sepsis, *STAR* Sepsis Transition and Recovery

^a^Only analyzed among Medicare-insured subgroup

The following secondary outcomes are assessed at 30 and 90 days after hospital discharge: all-cause mortality; all-cause, unplanned hospital readmission; cause-specific hospital readmissions with primary diagnoses (based on *International Classification of Diseases, 10th revision* diagnosis codes) related to sepsis or common infection (i.e., sepsis (A40–41, R65.20–21), pneumonia (J13–18), urinary tract infection (N30, N34, N39.0), skin and soft tissue infection (L00–08)), chronic lung disease (J40–47), heart failure (I50), and acute renal failure (N17); ED visits; acute care costs for services received at ED, inpatient, or observation encounters to any AH facility; total healthcare costs for inpatient and outpatient services received at any AH or outside system hospital or provider clinic (only in the subgroup of patients enrolled in a Medicare Shared Savings Plan with complete claims data tracked in AH EDW); and acute care-free days alive, defined as the sum of days alive without inpatient, observation, or ED encounters (rounded to a full day for any day with acute care utilization) during the interval after discharge. First, the total potential follow-up time is calculated as the number of days from index discharge to the earliest date of death or 30 (or 90) days post discharge (patients who die during their index hospitalization have 0 days alive). Each potential follow-up day is categorized as either an acute care day or an acute care-free day, based on any inpatient, observation, or ED encounter on that day. Total acute care-free days alive are calculated as the total potential follow-up time minus the number of acute care days during the 30 (or 90) days after index hospital discharge.

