### Statistical analysis

Primary analyses will follow an intent-to-treat approach such that patients will be analyzed based on the group to which they were initially randomized after exclusion of patients with infection ruled out during their hospitalization. We will assess the balance in the distributions of baseline covariates for patient factors (e.g., age, comorbidities), acuity (e.g., organ dysfunction, mechanical ventilation), length of stay, and discharge disposition (e.g., SNF, rehabilitation, home) between study groups. Comparisons of the two groups will be made using univariate analyses such as the *t* test and chi-square test.

The primary composite outcome, 30-day readmission and mortality, will be compared between the two arms using logistic regression. We will present the effects of the STAR program on the incidence of the composite readmission and mortality outcome as odds ratios and 95% confidence intervals. In addition to the primary intent-to-treat analysis, and since there is significant overlap between general AH Transition Services and the STAR program services integrated within AH Transition Services, we will conduct a modified intent-to-treat analysis excluding usual care patients who attended the AH Transition Services clinic during the 30 days after hospital discharge. Based on historical data, we anticipate an approximately 10% referral rate to AH Transition Services in the usual care group. Finally, we will complete a per-protocol analysis to compare patients in the STAR intervention arm who are eligible at hospital discharge and complete the 30-day STAR program to patients who are eligible at hospital discharge and receive usual care.

Secondary acute care and cost outcomes and process measures will be evaluated using the same approach. We will test different distribution parameters to determine the optimal distribution family for each model and outcome variable (e.g., gamma distribution for costs, Poisson distribution for acute care-free days). Any substantial changes to the study processes will be documented, discussed with investigators at monthly meetings, and incorporated into analyses of study outcomes. All hypothesis tests will be two sided and data will be analyzed using SAS Enterprise Guide v7.1 (Cary, NC, USA).

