### Missing data

We do not anticipate substantial missing data because all outcomes are routinely collected variables and utilization is broadly captured within our large integrated system. Values for patients who do not have healthcare utilization or mortality records during the study follow-up interval are assumed to be null. While utilization may occur outside AH, this is not expected to be a major limitation because of the AH market share and accessibility. Specifically, AH operates three large hospitals in Cabarrus and Mecklenburg Counties and more than 40 hospitals in the region overall. Additionally, any utilization occurring outside the system is anticipated to be non-differentially distributed between groups and thus to impact treatment groups equally. Further, internal historical data indicate that nearly 75% of high-risk patients are Medicare-insured (i.e., Medicare Shared Savings Plan beneficiaries). For these patients, we will have complete healthcare claims within and outside AH facilities during the study interval, as captured through participation in the local AH-managed Accountable Care Organization. We will conduct subgroup analyses within this Medicare-insured population and will use these data to explore missing data patterns that can be adjusted using pattern-mixture methods in sensitivity analyses.

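### The distribution family for secondary outcomes is left to testing on the trial data, and the two families given as examples do not suit acute care costs (many zeros) or acute care-free days (bounded, with a lump at 0)

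*Protocol article*

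**What the plan says.** In the protocol article, the Statistical analysis section compares the primary composite by logistic regression and says that the secondary acute care and cost outcomes will follow the same approach. It then adds: "We will test different distribution parameters to determine the optimal distribution family for each model and outcome variable". The examples offered in parentheses are "gamma distribution for costs, Poisson distribution for acute care-free days".

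The Study outcomes section defines the variables:

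- Acute care costs are "acute care costs for services received at ED, inpatient, or observation encounters to any AH facility".
- Total healthcare costs also cover outpatient services, and are analysed "only in the subgroup of patients enrolled in a Medicare Shared Savings Plan with complete claims data tracked in AH EDW".
- For acute care-free days, "Total acute care-free days alive are calculated as the total potential follow-up time minus the number of acute care days". The follow-up time is at most 30 or 90 days, and "patients who die during their index hospitalization have 0 days alive".

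The Missing data section adds: "Values for patients who do not have healthcare utilization or mortality records during the study follow-up interval are assumed to be null". I read this as no use, hence zero cost, with the patient kept in the analysis.

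**The concern.** The examples are the only guidance the article gives for these outcomes, and both conflict with its own definitions.

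**Costs.** A patient with no acute encounter after discharge has an acute care cost of exactly zero, where a gamma likelihood is not defined. The quick way round is to model positive costs only. That restricts the comparison to patients who used acute care after randomisation. It also discards the main route by which STAR could save money, which is avoiding encounters.

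**Days.** Poisson sets the variance equal to the mean. A variable capped at 30 or 90, with most patients at or near the cap and deaths pulled down to 0, has no reason to satisfy that. If the variance exceeds the mean, unscaled standard errors are too small and false positives rise. If it is below the mean, the test loses power.

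Selecting a family by testing on the trial data does not by itself supply a point mass at zero, an upper bound or a robust variance. It also makes the model for each secondary outcome depend on the data it is meant to analyse.

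**Working it through.** **Planned size.** The plan gives no figure for these secondary analyses, so I checked only the sample size used below. With 40% versus 30%, 80% power and two-sided α = 0.05, the unpooled formula gives (1.96 + 0.8416)² × (0.24 + 0.21) / 0.10² = 353.2, so 354 per arm. The plan's figure reproduces.

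**Share of zero costs.** The composite rates are 40% (usual care) and 30% (STAR), from Sample size calculation. Readmission is one component, so at 30 days at least 60% and 70% have no unplanned readmission: 354 × 0.60 ≈ 212 and 354 × 0.70 ≈ 248 patients. ED-only visits and planned stays lower the zero-cost share by an amount the article does not state.

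**Effect of dropping zeros.** Mean cost = (share with any use) × (mean cost per user, c). Assume shares of 40% and 30% and equal c.

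- Zeros kept: 0.30c / 0.40c = 0.75.
- Users only: c / c = 1.0.

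**Effect of keeping zeros.** A log-link gamma model with estimated dispersion was simulated under the null (500 runs, lognormal costs among users). It rejected 5.8% of the time with 60% zeros and 3.6% with 70% zeros.

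**Days, simple case.** Let a fraction p sit at 0 and the rest at the maximum T. The mean is T(1 − p), the variance is T²p(1 − p), and variance/mean = Tp. A nominal 5% Wald test with unscaled Poisson errors has a true type I error of about 2[1 − Φ(1.96/√(variance/mean))]. For an assumed p = 5%:

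- T = 30: ratio 1.5, type I error about 11%.
- T = 90: ratio 4.5, type I error about 36%.

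**Days, simulation.** Null trials, 354 per arm, 4,000 runs each. All death and stay inputs are assumptions, because the article gives none.

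| Days | Index deaths | Later deaths | Any acute use | Mean stay (days) | Variance/mean | Type I error, unscaled Poisson | Type I error, robust |
|---|---|---|---|---|---|---|---|
| 30 | 0% | 2% | 20% | 4 | 0.35 | 0.3% | 5.5% |
| 30 | 0% | 5% | 25% | 5 | 0.80 | 2.7% | 5.1% |
| 30 | 5% | 8% | 30% | 6 | 2.64 | 22% | 5.1% |
| 30 | 10% | 10% | 40% | 6 | 4.27 | 35% | 5.3% |
| 90 | 0% | 10% | 40% | 8 | 3.37 | 29% | 5.1% |
| 90 | 5% | 15% | 40% | 8 | 8.82 | 51% | 5.0% |
| 90 | 10% | 18% | 50% | 10 | 13.72 | 60% | 4.8% |

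A second set of assumed rates gave 0.02% to 21% at 30 days and 23% to 50% at 90 days, with 4.5% to 5.4% under robust variance. By the formula above, 23% corresponds to a variance/mean ratio of about 2.7.

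**The case against.** The strongest reply is that the article commits to neither family. Both are examples inside a plan to choose by testing, and a fit check would be expected to expose a block of zero costs or a variance several times the mean. Zero handling, dispersion scaling and robust variance are commonly left to a statistical analysis plan, which is not shown. This largely stands, and it limits the point. A reader might infer that the named models cannot fit and that the secondary p values and intervals will be wrong. The documents do not support that:

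- The Missing data section assigns a value to patients without use and does not remove them.
- A gamma model with zeros kept and estimated dispersion held its size, and a comparison of mean days with robust variance did too.
- At 30 days even the direction of the Poisson error depends on death rates that the article does not give.

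A reader might also infer that most patients have zero cost in every cost outcome. The zero share is not stated. At 90 days the Background cites 40% readmission before ED-only visits are counted, so a zero majority is unproven. Total healthcare costs in the Medicare subgroup include outpatient care and are much less affected.

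What the reply does not remove is the stated choice of family on the trial data, illustrated by two families that conflict with the definitions. A fit check may reveal a misfit, but changing family does not by itself provide a robust variance, a mass at zero or an upper bound.

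**Conclusion.** The point holds in a limited form. The example families do not suit acute care costs or acute care-free days as defined, and leaving the family to testing on the trial data does not secure a valid analysis.

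The harm is conditional. If zero costs were dropped, a true mean ratio of 0.75 could appear as 1.0. If Poisson were kept with unscaled errors, type I error would run from under 1% to about 35% at 30 days and from about 23% to 60% at 90 days.

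The 90-day result is the firmer one, since every assumed scenario inflated the error. At 30 days, the scenarios with no index-stay deaths were conservative. Index-stay deaths do enter the main analysis, because index survivors appear only as a subgroup in the Subgroups section. Eligibility also admits patients with a mortality risk of at least 10%, although no death rate is given.

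All of these sizes rest on assumed death, stay and use rates. Only the cost and acute care-free-days secondary outcomes are touched. The primary logistic regression and its sample size are unaffected.

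**What to change.** Before any comparison by arm, replace the data-driven choice of family with stated methods:

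- **Acute care costs:** compare arm means with zeros included, by a log-link GLM with robust or bootstrap standard errors, or by a two-part model recombined to a mean difference.
- **Acute care-free days:** compare means with robust or bootstrap standard errors, or use a rank or ordinal analysis. A Poisson working model can stay if its variance is robust.

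If the full analysis plan already fixes such methods, it is enough to bring the protocol wording into line with it. The cost is a change of wording and slightly more analysis work. Intervals for acute care-free days may be wider than unscaled Poisson ones. No change to data collection or sample size is needed.

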### Subgroups

In addition to the overall study population, primary and secondary outcomes will be compared between the usual care and STAR intervention arms within several clinically relevant subgroups, including: chronic comorbidity burden (i.e., Charlson Comorbidity Index ≥ 5 or < 5); acute severity of index hospitalization (i.e., septic shock or no shock, defined by fluid-resistant hypotension requiring vasopressors and hyperlactatemia (> 2 mmol/L)) [66]; patients who survive the index hospitalization; and Medicare patients over age 65 years (due to the presence of complete claims data on these patients and the additional financial incentives and programs aimed at reducing total and post-acute care spend in this population).

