### Study setting and population

This trial will occur at three facilities within AH, one of the largest, integrated healthcare delivery systems in the United States. The study population is depicted in Fig. 1 and includes adults admitted to the hospital from the Emergency Department (ED) who meet the following inclusion criteria: ≥ 18 years of age; oral or parenteral antibiotic or bacterial culture order within 24 h of ED presentation and either culture drawn first, antibiotics ordered within 48 h or antibiotics ordered first, culture ordered within 48 h (adapted from Third International Consensus Definitions for Sepsis and Septic Shock criteria) [30]; not discharged from the hospital at the time the daily list of eligible patients is generated each weekday morning; and deemed high risk for either 30-day readmission or mortality, defined as a readmission risk probability ≥ 20% or mortality risk probability ≥ 10%.

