At the initial telephone-based contact with the patient or caregiver during hospitalization, the STAR navigator introduces the STAR program and, in situations when the patient can participate, conducts a mental health screening using the Patient Health Questionnaire (PHQ)-2, with reflex administration of the PHQ-9 for positive PHQ-2 (i.e., ≥ 3 points on a scale of 0–6 points) [34]. The STAR navigator communicates the results to the patient’s attending physician. Additionally, the STAR navigator confirms consultations with physical therapy (with recommendation to consult delivered to the care team, if not in place), antibiotic stewardship (i.e., a coordinated program promoting appropriate antibiotic use with a pharmacist review of type and duration, with a review requested by the navigator if not completed), and an additional infectious disease specialist if ongoing systemic inflammatory response syndrome criteria are present more than 48 h after infection onset (i.e., at least two of the following clinical findings: body temperature < 36 °C or > 38 °C, heart rate > 90 beats/min, respiratory rate > 20 breaths/min, and white blood cell count < 4000/mm^3^ or > 12,000/mm^3^) [35, 36]. Finally, if the patient has a serious, chronic illness and either failure to improve after 5 days or a previous hospital admission in the last 60 days, the STAR navigator recommends a goals of care discussion led by the care team or a palliative care consultation [37]. Every 24–48 h during the remainder of the hospital stay, the STAR navigator reviews the patient’s electronic record, communicates with the patient or caregiver, and checks with the clinical case management team for updated discharge planning. Prior to discharge, the STAR navigator provides infection-specific education to the patient and caregiver, which also includes what to expect during transition from the hospital and written information on scheduled outpatient appointments and planned telephone touchpoints. The STAR navigator also reviews discharge orders and confirms inpatient pharmacist review of high-risk medications, including: appropriate indication if prescribed proton pump inhibitor, opioids, benzodiazapines, or antipsychotics; appropriate medications prescribed for chronic lung disease or chronic heart failure (e.g., inhaled corticosteroids for chronic lung disease; or diuretics, beta blockers, angiotensin-converting enzyme inhibitors, aspirin, or statins for chronic heart failure); and medication doses adjusted as needed if any new or worsening renal failure.

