We intentionally developed broad infection criteria to initially define adults with suspected serious infection or sepsis, with the additional application of our high-performing risk stratification models to objectively narrow the population to those at the highest risk of poor outcomes and with the potential to benefit most from added support. We anticipate that this approach will include a representative sample of patients with different chronic and acute problems. Because of the expected heterogeneity, we have defined a priori several subgroups of interest to further evaluate possible differential effects of the STAR program (e.g., patients with high comorbidity burden).

There are some limitations to this study. The results may not be generalizable to all sepsis survivors because study participants are enrolled from a single healthcare system. However, the inclusion of three heterogeneous hospitals within the healthcare system increases the applicability of our findings. Second, we did not protocolize the usual care arm, thus care provided to patients in this group may be variable or change over time. While this may increase noise in determining the true treatment effect, it is consistent with the concept of a pragmatic study design. The STAR program was developed in partnership with a multidisciplinary team of sepsis stakeholders and designed to be implemented and evaluated in a real-world setting. If effective, this program would offer a timely solution for hospitals facing potential financial penalties for higher-than-expected readmission rates and looming alternate payment models such as bundled payments and shared savings programs for Accountable Care Organizations, which creates incentives to deliver care in less intensive settings during the 90 days after hospitalization.

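### Subgroup effects are to be compared between arms within strata, which does not test the differential effects they are meant to evaluate; one subgroup is defined after randomisation and another may be

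*Protocol article*

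**What the plan says.** The Subgroups section of the protocol article states the method: "primary and secondary outcomes will be compared between the usual care and STAR intervention arms within several clinically relevant subgroups". It names four subgroups: Charlson Comorbidity Index 5 or more against less than 5; "acute severity of index hospitalization (i.e., septic shock or no shock", with shock defined by vasopressor need and raised lactate; "patients who survive the index hospitalization"; and Medicare patients older than 65. The first two are pairs of strata. The last two are named without a complementary stratum.

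The Discussion states the purpose: "we have defined a priori several subgroups of interest to further evaluate possible differential effects of the STAR program". Its example is high comorbidity burden.

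On timing, Study setting and population requires that a patient be "not discharged from the hospital at the time the daily list of eligible patients is generated each weekday morning", so randomisation takes place during the index stay. Trial interventions places the first STAR contact in the same stay: "At the initial telephone-based contact with the patient or caregiver during hospitalization, the STAR navigator introduces the STAR program". Under Study outcomes, deaths count towards the primary outcome from index presentation onwards, so index-stay deaths are events.

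Statistical analysis specifies logistic regression for the primary outcome, reported as odds ratios with 95% confidence intervals. The article mentions neither an interaction term nor any contrast between strata.

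**The concern.** A differential effect is a difference between two stratum-specific effects. Comparing arms inside each stratum answers another question, namely whether there is an effect in that stratum. One result below 0.05 and the other above it is what one would often see when the effect is the same in both strata and each stratum is underpowered. A health system could then direct STAR towards, or away from, patients with high comorbidity or shock on a contrast that is only noise.

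The survivor subgroup raises a separate problem. Membership is settled after randomisation and after STAR has begun. The inpatient STAR tasks (antibiotic stewardship review, infectious disease input, goals-of-care or palliative recommendations) could in principle affect who survives the stay. Survivors in the two arms are then not guaranteed to be comparable, and the restriction removes part of the primary outcome. Because the trial presents itself as one of sepsis survivors, this result will draw attention.

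**Working it through.** **Inputs.** From Sample size calculation: 40% (usual care) and 30% (STAR), 354 per arm, alpha 0.05. From Statistical analysis: two-sided tests. Assumed, because the article gives no Charlson or shock shares: stratum splits from 50:50 to 80:20 (75:25 also, for interaction power), equal in both arms, with 40% v 30% in each stratum.

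**Reproducing the plan's figure.** Unpooled sample size: (0.24 + 0.21) × (1.960 + 0.842)² / 0.10² = 354 per arm, as stated. With pooled variance under the null,

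power = Φ{[0.10 − 1.96 √(0.455/n)] / √(0.45/n)},

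where 0.455 = 2 × 0.35 × 0.65 and 0.45 = 0.24 + 0.21. At n = 354 this is 79.8%. The sample size is sound and plays no further part.

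**Same true effect in both strata.** Put each stratum's per-arm n into the power formula to get a and b. The chance that exactly one stratum is significant is a(1 − b) + b(1 − a).

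| Split | n per arm | Power a / b | Exactly one significant |
|---|---|---|---|
| 50:50 | 177 / 177 | 0.505 / 0.505 | 0.505×0.495 + 0.505×0.495 = 0.500 |
| 70:30 | 247.8 / 106.2 | 0.646 / 0.332 | 0.646×0.668 + 0.332×0.354 = 0.549 |
| 80:20 | 283.2 / 70.8 | 0.705 / 0.237 | 0.705×0.763 + 0.237×0.295 = 0.608 |

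A simulation of 200,000 trials per split, with Wald tests of the log odds ratio, gave 50.0%, 54.8% and 60.8%. In the same simulated trials a Wald interaction test was falsely significant about 5% of the time at each split.

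**No effect in either stratum.** Exactly one significant: 2 × 0.05 × 0.95 = 9.5% per pair, against about 5% for the interaction test.

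**Power of the interaction test.** For a 10-point difference between the two risk differences, SE = √(0.45/n₁ + 0.45/n₂) and power = Φ(0.10/SE − 1.96).

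- 50:50: SE = √(0.45/177 + 0.45/177) = 0.0713, power 29%.
- 75:25: SE = √(0.45/265.5 + 0.45/88.5) = 0.0823, power 23%.

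For 80% power the difference must be about 2.80 × SE: 20 points at 50:50 and 23 points at 75:25. This is on the risk-difference scale. The logistic interaction is on the log-odds scale, so these figures are a guide.

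**Timing of subgroup membership.**

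- *Charlson*: a comorbidity measure, fixed at baseline.
- *Medicare over 65*: appears to be fixed at baseline.
- *Survivors*: settled at the end of the index stay, after randomisation and first STAR contact. Certainly post-randomisation.
- *Shock*: described as severity of the index hospitalisation, with no cut-off at randomisation. Table 2 likewise records vasopressor receipt during the index hospitalisation. Possibly post-randomisation for some patients.

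**The case against.** The strongest reply is that this is a condensed article, and interaction tests, time windows and labels for exploratory results usually sit in an analysis plan that is not shown. That has force for the shock window. It does not dispose of the main point, because the article states both a method and a purpose, and they do not match.

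Several stronger readings are tempting, and the document does not support them:

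- *That heterogeneity will be declared from one significant and one non-significant stratum.* No such decision rule is written. The stated method merely leaves room for it.
- *That the planned analysis cannot show differential effects at all.* Odds ratios with intervals, side by side, allow an informal contrast for Charlson and shock.
- *That the mismatch covers all four subgroups.* Survivors and Medicare over 65 have no named complement, and the Medicare group is given other reasons (complete claims and payment incentives). The discordance figures apply to two subgroups.
- *That false contrasts will be common whatever STAR does.* The 50% to 61% range needs the full design effect; under a complete null it is 9.5%.
- *That there will be 126 subgroup tests (21 outcomes in Table 3 × 6 strata).* This is a ceiling. Two total-cost outcomes are restricted to Medicare patients, and nothing says every cell will be formally tested.
- *That shock is certainly post-randomisation.* The text is silent on this.
- *That the survivor analysis biases the main result.* The primary analysis keeps index-stay deaths as events, and subgroups are additional to it. The article gives no basis for sizing any bias in the survivor comparison.

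It is also fair to object that an interaction test would seldom detect a real difference here. That stands, and it limits what the remedy can deliver.

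**Conclusion.** The concern holds in a limited form. For Charlson and shock, the written method does not test the stated question. If STAR works as designed and equally in both strata, a misleading split in significance has a probability of about 50% to 61% over the assumed splits, against about 5% for an interaction test. These figures rest on equal event rates in the two strata and on shares that the article does not give.

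The survivor comparison is certainly conditioned on a post-randomisation event that forms part of the primary outcome, so randomisation does not protect it. For shock this is possible but not established. The primary analysis and the sample size are unaffected. This should be corrected before subgroup results are interpreted.

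**What to change.** 1. For the primary outcome, add a treatment-by-subgroup interaction term to the logistic model, one model for Charlson and one for shock. Base any claim of differential effect on that term, and report stratum odds ratios with 95% confidence intervals as exploratory.
2. Define shock from data available before randomisation.
3. Label the survivor analysis supportive, and always show it beside index-hospital mortality by arm.
4. Label subgroup results for secondary outcomes descriptive.
5. State that a non-significant interaction is not evidence of equal effects, given the low power shown above.

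The cost is wording in the protocol or analysis plan, plus time-stamped vasopressor and lactate data for item 2. No change to sample size, follow-up or the primary analysis is needed. The price in inference is that real differences of moderate size will usually go undetected, so the useful output will be estimates and their intervals.
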